#### To week 24 of follow-up

- Body weight
- Laboratory parameters
  GPT (=ALT), GOT (= AST), GGT,
  Other laboratory parameters:
  hemoglobin, platelets, WBC, neutrophils (%), bilirubin, creatinine, TSH, blood glucose (fasting), HbA1c, triglycerides, cholesterol, HDL, LDL, serum ferritin ANA, LKM, SMA, AMA, SLA, Trak, MAK, TSH, rheumatoid factors
- Hepatitis C laboratory diagnostic tests
  HCV-PCR (qualitative/quantitative) *only qualitative recommended*
- Hepatitis B laboratory diagnostic tests (only if chronic hepatitis B was documented at the baseline examination): HBsAg (+/-), HBeAG +/-; HBV-DNA quant./qual., anti-HBs (+/-); anti-HDV (+/-), HDV-RNA (+/-, qual. or quant.)
- Adverse events (including suspected cases) with substance-specific causality survey
- Concomitant medication
- Clinical symptoms: none, fatigue, fever, muscular stiffness, skin changes, hair loss, joint pain, muscle pain, abdominal pain, nausea, reflux, weight loss, headache, insomnia, irritability, restlessness, depression, depressive mood, psychosis, impaired concentration, anorexia, jaundice, pruritus, elevated GPT, craving / withdrawal-like symptoms, other treatment-related sick leave (duration) since the last examination
- Pregnancy
- Quality of life assessment compared to before treatment: symptom-free; improved, but not symptom-free; unchanged
- Alcohol consumption no/yes, if yes, inquiry ≤/ > 40 g/d and drinks/d in the last 30 days
- Submission of the SF-36 and sociodemography record form (questionnaire to be completed by the patient)

### Additional module for recording treatment of hepatitis C in opioid substituted patients

#### Baseline examination

- Addiction history (acc. to EuropASI)
- Substitution therapy: methadone, L-polamidone, buprenorphine, buprenorphine/naloxone combination, heroin, other, in each case stating the dose/day;
  on-site in the practice, in pharmacy: daily, how often per week / take-home, how often per week
- Urinalysis: no/yes, if yes then: -/+: cocaine, benzodiazepines, barbiturates, amphetamines, cannabis, methadone, L-polamidone, buprenorphine, heroin, EDDP, creatinine, if positive, then inquire about measured value
- Laboratory parameters:
  MCV, CRP quant., TPHA (syphilis), Mendel-Mantoux test (tuberculosis)
- Psychosocial care ( most probable):
- 1h/day, 1-2h/week, 1-2h/month, feedback 1x/quarter
- done by: substituting physician him/herself, qualified social education worker, psychologist, other specialist
- on-site in the practice, externally in DCC

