#### Examination after 2 weeks

- Urinalysis: no/yes, if yes then: -/+: cocaine, benzodiazepines, barbiturates, amphetamines, cannabis, methadone, L-polamidone, buprenorphine, heroin, EDDP, creatinine, if positive, then inquire about measured value
- Substitution therapy: methadone, L-polamidone, buprenorphine, buprenorphine/naloxone combination, heroin, other, in each case stating the dose/day;
  on-site in the practice, in pharmacy: daily, how often per week / take-home, how often per week

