#### Examinations during the treatment at week 4, 8, 12, 24, 36 48, at end of hepatitis C therapy/documentation

- Urinalysis: no/yes, if yes then: -/+: cocaine, benzodiazepines, barbiturates, amphetamines, cannabis, methadone, L-polamidone, buprenorphine, heroin, EDDP, creatinine, if positive, then inquire about measured value
- Substitution therapy: methadone, L-polamidone, buprenorphine, buprenorphine/naloxone combination, heroin, other, in each case stating the dose/day;
  on-site in the practice, in pharmacy: daily, how often per week / take-home, how often per week
- ***Only in week 24, 48 and at the end of hepatitis C therapy/documentation:***Substance use (acc. to EuropaASI, restricted to the consumption behaviour in the last 30 days)
- ***Only in week 24 and 48:*** Psychosocial care (most probable):
- 1h/day, 1-2h/week, 1-2h/month, feedback 1x/quarter
- done by: substituting physician him/herself, qualified social education worker, psychologist, other specialist
- on-site in the practice, externally in DCC

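### The psychosocial-care item in the opioid-substitution module has no answer for absence of care, and gives no on-treatment value for patients who stop before week 24

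*Protocol*

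**What the plan says.** Section 7.2.3 of the Protocol lists psychosocial care in three places: baseline, the on-treatment block, and week 24 of follow-up. Each listing has the same three parts:

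- intensity: "1h/day, 1-2h/week, 1-2h/month, feedback 1x/quarter"
- provider: "done by: substituting physician him/herself, qualified social education worker, psychologist, other specialist"
- place: "on-site in the practice, externally in DCC"

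The on-treatment block is headed "Examinations during the treatment at week 4, 8, 12, 24, 36 48, at end of hepatitis C therapy/documentation". Within it, the entry beginning "Psychosocial care (most probable" is restricted to "Only in week 24 and 48". The entry just above it, on substance use, is asked at weeks 24 and 48 and also at end of therapy. The separate "Examination after 2 weeks" contains urinalysis and substitution therapy only.

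Other items in the same module do have an explicit negative. Urinalysis is set out as "Urinalysis: no/yes, if yes then: -/+: cocaine, benzodiazepines, barbiturates" and so on, and at follow-up substitution therapy has an answer for patients who no longer receive it.

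Three other sections bear on the point. Section 7.2 says that the headings do not oblige the physician to investigate every parameter. Section 8.3 plans absolute and relative frequencies for categorical data. Section 9 promises a descriptive presentation of all recorded variables.

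**The concern.** A patient without psychosocial care has no valid answer. The physician can leave the item empty, in which case the record looks the same as one where nobody asked. Or the physician can tick the nearest positive category, in which case the record is wrong. Either way, the frequency table for this item cannot show how many substituted patients had no psychosocial care.

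The visit schedule adds a second, separate gap. Patients whose treatment ends before week 24 pass through the module without an on-treatment value, although they do have an end-of-therapy visit at which one could be recorded. On-treatment care is thus described only in patients who remained on treatment to week 24 or beyond.

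At stake is the completeness of one descriptive variable in a group that section 4.3 names as a reason for the open design (addiction patients), in a study whose aims (section 4.2) include therapeutic habits and quality of treatment.

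**Working it through.** The protocol states no figure for this item, so there is none to reproduce. The check is a reading of every listing and a count.

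**Answer categories (7.2.3).**

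| Listing | Intensity options | Options meaning no care | No/yes gate |
| --- | --- | --- | --- |
| Baseline | 4 | 0 | no |
| Weeks 24 and 48 | 4 | 0 | no |
| Follow-up week 24 | 4 | 0 | no |

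The provider list (four types) and the place list (two places) have no negative answer either.

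**What a blank can mean.** Let N be the number of patients with the module form at a visit, a the number with an answer, n0 the number truly without care and m the number not documented for other reasons.

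- If every patient without care is left blank, then N − a = n0 + m. Only the sum is observed, so the share without care, n0/N, can lie anywhere from 0 to (N − a)/N.
- If some patients without care are put into a positive category, even (N − a)/N is no longer an upper limit.
- If percentages are taken over a alone, the table shows 0% without care whatever the truth is.

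**On-treatment visits (7.2.3).** The scheduled visits from week 2 on are weeks 2, 4, 8, 12, 24, 36 and 48 and end of therapy, 8 in all. Psychosocial care is listed at 2 of them. The largest possible number of on-treatment values is:

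| Length of treatment | Values |
| --- | --- |
| Stop at or before week 12 | 0 |
| 16-week course | 0 |
| Any other stop before week 24 | 0 |
| 24 weeks | 1 if the week-24 form is used, 0 if only the end-of-therapy form is |
| Stop between weeks 24 and 48 | 1 |
| 48 weeks | 2, or 1 if week 48 is recorded only as end of therapy |
| 72 weeks | 2, none after week 48 |

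Section 4.1.3 itself foresees treatment ending before week 24: a decision at week 12 whether to continue, and 16-week courses in some patients with genotype 2 or 3. Section 6.1 requires concluding documentation for every patient, also after discontinuation. So the end-of-therapy form exists for these patients, but this item is not on it.

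**Can another item fill the gap?** The practice characteristics in 7.2.1 record regular cooperation with psychiatrists, psychologists or an external drug counselling centre. That is per practice and gives no patient-level value.

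**The case against.** Several counter-arguments have weight.

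- **Queries.** Under 10.3.2 forms are checked for completeness and discrepancies are clarified with the physician. Under section 11 incomplete visits are queried and are not paid if they remain incomplete. A blank in all three parts of the item can therefore be noticed. But a query does not create a category for its answer: the physician who replies that there is no care still has nothing to tick. The payment rule may even favour ticking the lowest intensity, although the protocol does not say how an empty optional item counts.
- **The eCRF is not shown.** The screens may contain a further option. The finding concerns the categories that the protocol lists.
- **Recording burden.** Weeks 24 and 48 match the standard course lengths, and asking a background item rarely is a legitimate choice. It is not a contradiction. It does leave shorter courses and early stops uncovered.
- **Timing.** This version is dated 28.02.2013, and section 5.2 closes the treatment-decision window on 31 December 2011. For a patient who started on that day, week 24 (168 days) fell on 16 June 2012 and week 48 (336 days) on 1 December 2012. If enrolment closed as planned, a form change now reaches mainly late end-of-therapy and follow-up visits. This stands, and it is why the fix includes a reporting rule.

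A reader might infer that care cannot be compared between early stoppers and completers. The documents do not support that. Baseline care is listed for everyone in the module, so the comparison can be made with baseline values, subject to the missing 'none' category. Nor is it a stated objective. A reader might also want a percentage by which the category shares are inflated. That needs the share of patients without care, which the protocol does not give, and it needs all such patients to be left blank and blanks to be dropped from the denominator. Section 8.3 fixes no such denominator.

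**Conclusion.** The point holds, at low importance. As listed, the item cannot separate absence of psychosocial care from non-documentation at any of its four time points (baseline, weeks 24 and 48, follow-up), so the share of patients without care cannot be reported. Separately, patients who stop before week 24 have 0 on-treatment values, while those who stop between weeks 24 and 48 can have one. Baseline values remain for all, and follow-up values for those who are seen.

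This rests on the protocol's list being the full set of eCRF answers and on the optional status of items in section 7.2. The number of patients affected cannot be stated: the protocol gives neither the size of the module nor the share without care. Virological outcomes and the main safety data are untouched.

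**What to change.** 1. In 7.2.3, add a 'none' answer to the intensity list, or put a no/yes gate before it as for urinalysis, at baseline, weeks 24 and 48 and follow-up week 24.
2. List the item at the end-of-therapy visit as well, in line with the substance-use entry in the same block.
3. For visits already entered, report blanks as a separate category and take percentages over all patients with the module form at that visit, not over answered items only. State in the report that no answer for absent care was available and that some patients without care may sit in a positive category.

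The cost is one answer option and one repeated item. The module's end-of-treatment visit is already paid at EUR 24.49 (factor 1.4), the same as weeks 24, 48 and follow-up, which carry the item. The drawback is that the new category will not be comparable with visits recorded before the change, so the two periods should be shown apart. Given the dates, item 3 will do most of the work in this study. Items 1 and 2 help only visits still outstanding and any later use of the form.

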#### Examination after 2 weeks

- Urinalysis: no/yes, if yes then: -/+: cocaine, benzodiazepines, barbiturates, amphetamines, cannabis, methadone, L-polamidone, buprenorphine, heroin, EDDP, creatinine, if positive, then inquire about measured value
- Substitution therapy: methadone, L-polamidone, buprenorphine, buprenorphine/naloxone combination, heroin, other, in each case stating the dose/day;
  on-site in the practice, in pharmacy: daily, how often per week / take-home, how often per week

#### Examinations during the treatment at week 4, 8, 12, 24, 36 48, at end of hepatitis C therapy/documentation

- Urinalysis: no/yes, if yes then: -/+: cocaine, benzodiazepines, barbiturates, amphetamines, cannabis, methadone, L-polamidone, buprenorphine, heroin, EDDP, creatinine, if positive, then inquire about measured value
- Substitution therapy: methadone, L-polamidone, buprenorphine, buprenorphine/naloxone combination, heroin, other, in each case stating the dose/day;
  on-site in the practice, in pharmacy: daily, how often per week / take-home, how often per week
- ***Only in week 24, 48 and at the end of hepatitis C therapy/documentation:***Substance use (acc. to EuropaASI, restricted to the consumption behaviour in the last 30 days)
- ***Only in week 24 and 48:*** Psychosocial care (most probable):
- 1h/day, 1-2h/week, 1-2h/month, feedback 1x/quarter
- done by: substituting physician him/herself, qualified social education worker, psychologist, other specialist
- on-site in the practice, externally in DCC

#### At week 24 of follow-up

- Urinalysis: no/yes, if yes then: -/+: cocaine, benzodiazepines, barbiturates, amphetamines, cannabis, methadone, L-polamidone, buprenorphine, heroin, EDDP, creatinine, if positive, then inquire about measured value
- Substance use (acc. to EuropaASI, restricted to the consumption behaviour in the last 30 days)
- Substitution therapy: methadone, L-polamidone, buprenorphine, buprenorphine/naloxone combination, heroin, other, in each case stating the dose/day;
  on-site in the practice, in pharmacy: daily, how often per week / take-home, how often per week
  "Patient no longer receives substitution therapy (e.g. because patient is "clean")"
- Psychosocial care ( most probable):
- 1h/day, 1-2h/week, 1-2h/month, feedback 1x/quarter
- done by: substituting physician him/herself, qualified social education worker, psychologist, other specialist
- on-site in the practice, externally in DCC

### Additional module for recording therapy of hepatitis C in HIV coinfected patients

#### Baseline examination

At the start of treatment with peg­interferon alfa-2a (Pegasys®) (baseline), the following parameters were recorded for patients with detected HIV infection:

- First HIV diagnosis (year), if known
- Route of transmission of HIV (mode of infection): illicit drugs (intravenous), MSM, heterosexual, unknown, other.
- Stage of disease (CDC)
- Previous diseases: AIDS-defining events
- Antiretroviral pretreatment: ART-naive / previously treated (*excluding current ART*)

If previously treated: start of first ART (antiretroviral treatment)

- - The patient was previously treated with [number of] ART regimens.
  - The patient was already treated with the following ART classes.

NRTI

NNRTI

PI

FI

Integrase inhibitor

CCR5 antagonist

- Resistance situation (FASTA file)
- Clinical laboratory tests:
  HIV-RNA, CD4 / CD8 cell count (absolute and %, including following visits), LDL, HDL, VLDL (fasting)
- Antiretroviral treatment including treatment pauses and reasons for start, change or discontinuation
- Patient compliance with antiretroviral medication
- Tolerability of antiretroviral medication (signature tox.)
- Concomitant medication: lipid reducers, antimycotics, tuberculostatics, antdiarrheals, antacids

#### Examinations during treatment in week 12, 24 and 48, at the end of hepatitis C treatment/documentation and in week 24 of follow-up

- Antiretroviral treatment including treatment pauses and reasons for start, change or discontinuation
- Clinical laboratory tests:
  HIV-RNA, CD4 / CD8 cell count, LDL, HDL, VLDL (fasting)
- Resistance situation, if appropriate (FASTA file)
- Patient compliance with antiretroviral medication
- Tolerability of antiretroviral medication (signature tox.)
- Concomitant medication: lipid reducers, antimycotis, tuberculostatics, antdiarrheals, antacids

### Additional module to record treatment of hepatitis C in patients with cardiovascular risk

#### Baseline examination

- Metabolic syndrome

**Definition according to WHO (1999):**

*Glucose intolerance, impaired glucose tolerance (IGT) or diabetes mellitus and/or insulin resistance together with two or more of the other criteria listed below:*

Criteria:

- Impaired glucose regulation or diabetes
- Insulin resistance (highest quartiles of the HOMA-IR index)
- Dyslipidemia:

Triglycerides:  150 mg/dl (1.7 mmol/l) and/or

HDL cholesterol: ♂:< 35 mg/dl (0.9 mmol/l), ♀: < 39 mg/dl (1.0 mmol/l)

- Hypertension:  140/90 mm Hg and/or corresponding treatment
- Central obesity: waist-to-hip ratio: ♂: > 0.9, ♀: > 0.85 and/or BMI  30 kg/m2

Microalbuminuria:  20 µg/min or ≥ 30 mg/g creatinine (albumin-to-creatinine ratio)

or

**Definition acc. to NCEPIIIATP (2001) synonym ATP III:**

Criteria:

- Hypertriglyceridemia:  150 mg/dl (1.7 mmol/l)
- Lowered HDL cholesterol: ♂:< 40 mg/dl, ♀: < 50 mg/dl
- Hypertension: ≥ 130/85 mm Hg and/or corresponding treatment
- Central obesity: BMI > 30 kg/m2 or waist: ♂: > 102 cm, ♀: >88 cm

Elevated fasting plasma glucose: ≥ 110 mg/dl (6.1 mmol/l)

or

**Definition acc. to IDF (2005):**

*Central obesity defined as: waist: ♂: > 94 cm (European), ♀: >80 cm (European) + 2 of the following criteria*

*Central obesity defined as: waist: ♂: > 90 cm (Asian), ♀: >80 cm (Asian) + 2 of the following criteria*

*Central obesity defined as: waist: ♂: > 85 cm (Japanese), ♀: >90 cm (Japanese) + 2 of the following criteria*

*For South and Central Americans the values for Asians are used.*

*For Africans, Mediterranean inhabitants and inhabitants of the Middle East the values for Europeans are used.*

Criteria:

- Hypertriglyceridemia:  150 mg/dl (1.7 mmol/l) or corresponding treatment
- Lowered HDL cholesterol: ♂:< 40 mg/dl (0.9 mmol/l), ♀: < 50 mg/dl (1.1 mmol/l) or corresponding treatment
- Hypertension: ≥ 130/85 mm Hg or corresponding treatment
- Elevated fasting plasma glucose: ≥ 100 mg/dl (5.6 mmol/l) or type 2 diabetes
- Diabetes mellitus type
- Overweight
- Blood pressure parameters
- Hip and waist circumference (calculation of waist-to-hip ratio)
- Smoker:
  1. currently smoking: patients who have previously smoked ³ 100 cigarettes and are currently smoking.
  2. former smokers: patients who have previously smoked ³ 100 cigarettes and are currently not smoking.
  Nonsmokers:
  patients who have previously smoked < 100 cigarettes.
- Laboratory parameters:
  Na, K, Ca, insulin (fasting)
  (Calculation of the HOMA-IR index:
  [fasting insulin (in mIU/l) x fasting plasma glucose (in mmol/l)/ 22.5]
  or
  [fasting insulin (in mIU/l) x fasting plasma glucose (in mg/dl)/ 405]),
  (repeat presentation of HbA1c, HDL, LDL, triglycerides, cholesterol (total), glucose (fasting), uric acid, BMI)
- Special concomitant medication

Diabetes: insulins and insulin analogues, oral antidiabetics (e.g. alpha-glucosidase inhibitors, biguanide derivatives, sulfonylurea derivatives, "glinides", "glitazones")

Hypertension: antihypertensives (e.g. ACE inhibitors, angiotensin II antagonists, centrally acting antihypertensives, beta blockers, calcium channel blockers, diuretics, combination products)

Dyslipidemia: lipid reducers (e.g. HMG-CoA reductase inhibitors, fibrates, nicotinic acid and derivatives,

Obesity: e.g. lipase inhibitors, appetite suppressants

- Familial history: diseases such as hypertension, myocardial infarction, stroke

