**Definition acc. to IDF (2005):**

*Central obesity defined as: waist: ♂: > 94 cm (European), ♀: >80 cm (European) + 2 of the following criteria*

*Central obesity defined as: waist: ♂: > 90 cm (Asian), ♀: >80 cm (Asian) + 2 of the following criteria*

*Central obesity defined as: waist: ♂: > 85 cm (Japanese), ♀: >90 cm (Japanese) + 2 of the following criteria*

*For South and Central Americans the values for Asians are used.*

*For Africans, Mediterranean inhabitants and inhabitants of the Middle East the values for Europeans are used.*

Criteria:

- Hypertriglyceridemia:  150 mg/dl (1.7 mmol/l) or corresponding treatment
- Lowered HDL cholesterol: ♂:< 40 mg/dl (0.9 mmol/l), ♀: < 50 mg/dl (1.1 mmol/l) or corresponding treatment
- Hypertension: ≥ 130/85 mm Hg or corresponding treatment
- Elevated fasting plasma glucose: ≥ 100 mg/dl (5.6 mmol/l) or type 2 diabetes
- Diabetes mellitus type ???
- Overweight
- Blood pressure parameters
- Hip and waist circumference (calculation of hip/waist ratio)
- Smoker:
  1. currently smoking: patients who have previously smoked ³ 100 cigarettes and are currently smoking.
  2. former smokers: patients who have previously smoked ³ 100 cigarettes and are currently not smoking.
  Nonsmokers:
  patients who have previously smoked < 100 cigarettes.
- Laboratory parameters:
  Na, K, Ca, insulin (fasting)
  (Calculation of the HOMA-IR index:
  [fasting insulin (in mIU/l) x fasting plasma glucose (in mmol/l)/ 22.5]
  or
  [fasting insulin (in mIU/l) x fasting plasma glucose (in mg/dl)/ 405]),
  (repeat presentation of HbA1c, HDL, LDL, triglycerides, cholesterol (total), glucose (fasting), uric acid, BMI)
- Special concomitant medication

Diabetes: insulins and insulin analogues, oral antidiabetics (e.g. alpha-glucosidase inhibitors, biguanide derivatives, sulfonylurea derivatives, "glinides", "glitazones")

Hypertension: antihypertensives (e.g. ACE inhibitors, angiotensin II antagonists, centrally acting antihypertensives, beta receptor blockers, calcium channel blockers, diuretics, combination products)

Dyslipidemia: lipid reducers (e.g. HMG-CoA reductase inhibitors, fibrates, nicotinic acid and derivatives),

Obesity: e.g. lipase inhibitors, appetite suppressants

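### In the cardiovascular module the IDF HDL cut-offs differ between mg/dl and mmol/l, and the later visits name a hip/waist ratio where the WHO criterion uses waist-to-hip

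*Protocol*

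**What the plan says.** Section 7.2.5 (additional module, cardiovascular risk) lists three alternative definitions of metabolic syndrome. It does so once for baseline and once for the later visits: weeks 24 and 48, end of therapy, and week 24 of follow-up.

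- **IDF (2005), HDL criterion:** men below "40 mg/dl (0.9 mmol/l", women below "50 mg/dl (1.1 mmol/l", or corresponding treatment. The same figures stand at baseline and at the later visits.
- **WHO (1999), HDL criterion:** men below "35 mg/dl (0.9 mmol/l", women below "39 mg/dl (1.0 mmol/l", again the same at both places.
- **ATP III (2001), HDL criterion:** men below 40 and women below 50, in mg/dl only.
- **WHO central obesity:** a waist-to-hip ratio above 0.9 (men) or 0.85 (women), and/or a BMI criterion, at baseline and at later visits.
- **Ratio to be derived from the circumferences:** at baseline "calculation of waist-to-hip ratio"; at the later visits "calculation of hip/waist ratio".

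Section 8.3 has categorical characteristics reported as absolute and relative frequencies. Section 9 commits the report to a descriptive presentation of every recorded variable.

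**The concern.** A threshold printed in two units should be one threshold. Here the IDF HDL limit in mmol/l is lower than the limit in mg/dl, so the same blood value can meet the criterion or miss it depending on the unit in which the laboratory reports. The protocol prescribes no unit and plans about 600 centres, so both may plausibly occur.

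The ratio is a separate matter. If a hip/waist value were set against a cut-off written for waist-to-hip, the comparison would run in the wrong direction, and only from week 24 onward. These are classification rules among the survey variables, and the resulting frequencies would go into the report.

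**Working it through.** **1. Conversion factor implied by each HDL pair (mg/dl divided by mmol/l)**

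| Pair | Calculation | Implied factor | Range allowing for rounding (±0.5 mg/dl, ±0.05 mmol/l) |
| --- | --- | --- | --- |
| WHO men | 35 / 0.9 | 38.9 | 36.3 to 41.8 |
| WHO women | 39 / 1.0 | 39.0 | 36.7 to 41.6 |
| IDF men | 40 / 0.9 | 44.4 | 41.6 to 47.6 |
| IDF women | 50 / 1.1 | 45.5 | 43.0 to 48.1 |

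The factor must be the same in all four rows. The women's ranges do not overlap. The men's IDF range meets the WHO ranges only at their extreme edge. Rounding therefore does not explain the gap.

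**2. What the IDF limits should be.** The WHO pairs give a factor of 38.9 to 39.0; I take 38.5 to 39.0 as an assumed range.

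- 40 mg/dl: 40 / 39.0 = 1.03 to 40 / 38.5 = 1.04 mmol/l (printed: 0.9)
- 50 mg/dl: 50 / 39.0 = 1.28 to 50 / 38.5 = 1.30 mmol/l (printed: 1.1)
- 0.9 mmol/l: 34.6 to 35.1 mg/dl (printed: 40)
- 1.1 mmol/l: 42.4 to 42.9 mg/dl (printed: 50)

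**3. Who is classified differently.** Men between about 35 and 40 mg/dl and women between about 42.5 and 50 mg/dl meet the criterion in mg/dl and miss it in mmol/l. For example, a man at 38 mg/dl is below 40, but 38 / 38.9 = 0.98 mmol/l is not below 0.9. A woman at 46 mg/dl is below 50, but 46 / 38.9 = 1.18 mmol/l is not below 1.1.

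**4. The other two-unit figures in the module.** Triglycerides: 150 / 1.7 = 88.2, the same pair in the WHO, ATP III and IDF lists. Glucose: 110 / 6.1 = 18.0 and 100 / 5.6 = 17.9. HOMA-IR constants: 405 / 22.5 = 18.0. These are consistent, so the unit error is confined to the IDF HDL pairs.

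**5. The ratio.** Hip/waist is the reciprocal of waist-to-hip. Hip/waist exceeds 0.9 whenever waist-to-hip is below 1 / 0.9 = 1.11, and exceeds 0.85 whenever waist-to-hip is below 1 / 0.85 = 1.18. A man with waist-to-hip 0.80 is negative at baseline; his hip/waist is 1 / 0.80 = 1.25, which would count as positive later if set against 0.9.

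**The case against.** Several points on the other side stand.

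- A reader might infer that the metabolic-syndrome thresholds are wrong as a set. They are not: the WHO HDL, triglyceride, glucose and HOMA-IR figures all agree.
- A reader might infer that classification by HDL drifts between visits. It does not: the IDF mismatch is identical at baseline and later.
- A reader might infer that the hip/waist wording produces an artificial rise in metabolic syndrome during antiviral treatment. The protocol does not support that. It never says that the later ratio is compared with the WHO cut-off, and the WHO criterion for those same visits still reads waist-to-hip, so a slip of wording is at least as plausible. Even a literal comparison would touch only the WHO definition; ATP III and IDF use waist circumference or BMI. The WHO central-obesity criterion can also be met through BMI, and the syndrome further requires a glucose or insulin-resistance abnormality plus at least two other criteria.
- A reader might want a percentage of patients misclassified. The protocol gives no HDL distribution. A share of patients in the discordant band would rest on assumed means and standard deviations, and would still not be the share whose syndrome label changes, because IDF needs central obesity plus two further criteria and accepts corresponding treatment in place of the HDL value.
- Metabolic syndrome is not among the stated objectives or the main parameters of interest. This protocol version dates from February 2013, after planned enrolment ended in December 2011, so new form text would reach few remaining visits.

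These points limit the consequence. They do not remove either contradiction: the IDF pairs cannot both hold, and the later-visit ratio conflicts with its own criterion.

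**Conclusion.** The point holds in limited form. The IDF HDL cut-offs are internally inconsistent at every visit: 0.9 and 1.1 mmol/l are printed where the module's own WHO conversion gives about 1.03 and 1.29. The affected bands are about 35 to 40 mg/dl in men and 42.5 to 50 mg/dl in women. The label changes only when HDL decides the criterion count and the patient is not on corresponding treatment.

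The later-visit ratio is named the wrong way round for the WHO criterion. It does harm only if taken literally, and then only to that criterion.

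The HDL result rests on the document's own figures, with an assumed factor range of 38.5 to 39.0 that does not alter the conclusion. The number of patients affected cannot be derived from the protocol. Inequality signs missing from the text as read were not counted. The effect stays within one descriptive additional module; the main efficacy and safety objective is unaffected.

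**What to change.** - Reconcile the IDF HDL pairs at baseline and later visits so that both units state the same threshold. If the mg/dl values are the intended ones, as their agreement with the ATP III list suggests, the mmol/l values become about 1.03 (men) and 1.29 (women).
- Name waist-to-hip as the ratio to be calculated at every visit.
- When metabolic syndrome is reported, apply the corrected thresholds to the recorded HDL and circumference values, with HDL brought to one unit first.

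The cost is a few corrected figures and words in Section 7.2.5 and one derivation rule in the analysis. No new data are needed: HDL and both circumferences are already survey variables, so patients already documented can be reclassified wherever those values were entered with an identifiable unit.
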